## Abstract

**Background:**

Podoconiosis is one of the forgotten types of leg swelling (elephantiasis) in the tropics. Unlike the other, better-known types of leg swelling, podoconiosis is not caused by any parasite, virus or bacterium, but by an abnormal reaction to minerals found in the clay soils of some tropical highland areas. Non-governmental Organizations (NGOs) have been responsible for the development of simple treatment methods without systematic evaluation of its effectiveness. It is essential that a large scale, fully controlled, pragmatic trial of the intervention is conducted. We aim to test the hypothesis that community-based treatment of podoconiosis lymphoedema reduces the frequency of acute dermatolymphangioadenitis episodes (‘acute attacks’) and improves other clinical, social and economic outcomes.

**Methods/Design:**

This is a pragmatic, individually randomised controlled trial. We plan to randomly allocate 680 podoconiosis patients from the East Gojjam Zone in northern Ethiopia to one of two groups: ‘Standard Treatment’ or ‘Delayed Treatment’. Those randomised to standard treatment will receive the hygiene and foot-care intervention from May 2015 for one year, whereas those in the control arm will be followed through 2015 and be offered the intervention in 2016. The trial will be preceded by an economic context survey and a Rapid Ethical Assessment to identify optimal methods of conveying information about the trial and the approaches to obtaining informed consent preferred by the community. The primary outcome will be measured by recording patient recall and using a simple, patient-held diary that will be developed to record episodes of acute attacks. Adherence to treatment, clinical stage of disease, quality of life, disability and stigma will be considered secondary outcome measures. Other outcomes will include adverse events and economic productivity. Assessments will be made at baseline and at 3, 6, 9 and 12 months thereafter.

**Discussion:**

The evidence is highly likely to inform implementation of the new master plan for integrated control of Neglected Tropical Diseases (NTDs), in which podoconiosis is identified as one of eight NTDs prioritised for control. Potentially, an estimated 3 million patients in Ethiopia will therefore benefit from the results of this trial.

**Trial registration:**

International Standard Randomised Controlled Trial Number. Registration number: ISRCTN67805210. Date of registration: 24 January 2013.

## Background

Podoconiosis is a form of lymphoedema (leg swelling) arising in people going barefoot in highland tropical areas [1]. It is a significant problem in tropical Africa where irritant soils have been generated by environmental conditions of high altitude (>1,000m) and high rainfall (>1,000mm per annum), and are farmed by very poor people who cannot afford shoes or water for washing [2]. Although rarely a direct cause of mortality, it disables an estimated 4 million subsistence farmers in tropical Africa, greatly reducing productivity [3], leading to significant stigma from the community [4–6] as well as health professionals [7], and low quality of life [8]. Despite the high impact of podoconiosis on rural farming communities, treatment has been hampered by misdiagnosis (chiefly confusion with filarial lymphoedema) and fatalism [7]. Only recently has any form of treatment been offered to people with podoconiosis, and this has grown up from grassroots level without systematic evaluation.

At present, foot hygiene services are offered to a total of about 60,000 patients by non-government organisations in three regions in Ethiopia. While one non-controlled follow-up study has assessed clinical and quality of life changes [9], the impact of the intervention has not yet been evaluated through a formal trial. It is important that fully controlled evaluation with measurement of a wider range of outcomes now happens, before the intervention is expanded to an additional 300 *woredas* (districts) in which podoconiosis was found to be prevalent in a recent nationwide mapping [10]. The evidence generated from this trial will be conveyed through a dissemination workshop to key government and non-government stakeholders once analysis is complete and is highly likely to inform implementation of the new master plan for integrated control of Neglected Tropical Diseases (NTDs), in which podoconiosis is identified as one of 8 NTDs prioritised for control. Potentially, an estimated 3 million patients in Ethiopia will therefore benefit from the results of this trial.

### Objectives

The primary objective of the trial is to test the hypothesis that community-based treatment of podoconiosis lymphoedema reduces the frequency of acute dermatolymphangioadenitis episodes (ADLA, ‘acute attacks’). The secondary objective is to test the hypothesis that community-based treatment of podoconiosis lymphoedema improves other clinical, social and economic outcomes.

### Endpoints

The endpoints for this trial are listed in Table 1.

**Table 1 Tab1:** Endpoints

	Endpoint details
Primary endpoint	Cumulative incidence of ADLA (total number of incident episodes over the 12-month follow-up period).
Secondary endpoints	Adherence to treatment
	Foot washing, use of ointment, use of bandages, elevation, exercises, use of socks and shoes.
	Clinical outcomes:
	Clinical stage of disease^a^
	Lower leg and foot circumferences^b^
	Presence of mossy changes
	Wounds and inter-digital lesions;
	Duration of ADLA days
	Social outcomes:
	Quality of life^c^
	Perceived stigma^d^
	Economic outcomes:
	Economic productivity^e^

ADLA, acute dermatolymphangioadenitis

^a^Using a scale specifically developed for use in podoconiosis patients [22]

^b^Measured in centimetres at mid-calf and mid-foot

^c^Using validated Amharic translation of Dermatology Life Quality Index [23] and WHO Disability Assessment Schedule-II (WHODAS-II)

^d^Using scale developed to measure stigma among podoconiosis patients (24)

^e^Other measures of economic vulnerability found to be related to podoconiosis in economic context survey

## Methods/Design

### Trial design

This is a pragmatic Randomised Controlled Trial (RCT) with two arms that will compare podoconiosis lymphoedema management in the community with delayed treatment (as the control).

### Study setting

The study will be based at the recently founded International Orthodox Christian Charities (IOCC) Debre Markos Podoconiosis Project [11] in northern Ethiopia. The protocol will be carried out in Aneded *woreda*, with an estimated total population of 89,446 [12], and made up of 19 *kebeles* (smallest administrative sub-unit) each with an average population of approximately 5,000 people and two Health Centres.

### Participants

Participants will be drawn from adults aged 18 years and older registered as affected with podoconiosis in Aneded *woreda*, East Gojjam Zone. These patients are representative of all those in Amhara regional state in northern Ethiopia, where the prevalence of podoconiosis is estimated as 3.4 % in the adult population [13]. Until 2010, there was no government or private treatment for podoconiosis anywhere in the region. In 2010, a podoconiosis project was established by IOCC and began treatment of 200 patients. To date, approximately 1,000 patients have been treated, and thousands more are on the waiting list for treatment [13]. Podoconiosis patients from nine *kebeles* of Aneded *woreda* will be invited to participate. Diagnosis of podoconiosis is currently based on clinical features: history of aching and burning starting in the feet, swelling progressing from the forefoot up the leg; patients must have lived for at least 10 years in communities 1,500 meters above sea level; and filarial lymphoedema must have been excluded (negative Binax-Filariasis rapid antigen test). Among people with lymphoedema in areas in which mass drug administration for lymphatic filariasis has never occurred, a negative rapid antigen test has high predictive value for podoconiosis.

### Eligibility criteria

The Inclusion, exclusion and withdrawal criteria are presented in Table 2.

**Table 2 Tab2:** Inclusion, exclusion and withdrawal criteria

Inclusion criteria	
1.	Be at least 18-years old
2.	Have provided informed consent
3.	Have a diagnosis of at least Stage 2 podoconiosis (that is, podoconiosis lymphoedema) confirmed by the trial team
4.	Have a negative ICT card test
5.	Intends to remain within the area during the study period
Exclusion criteria	
1.	Already undertaking self-treatment comparable to the intervention
2.	Nodular disease preventing use of shoes (will be referred for nodulectomy)
3.	Complex wounds (will be referred for specialist care in Debre Markos Hospital)
4.	Patient has a history of allergic reaction to treatment materials
5.	Mental health or learning disorder affecting ability to adhere with treatment
6.	Physical disability beyond podoconiosis precluding attendance at group sessions
7.	Disease considered by the Trial Co-ordinator to affect ability to self-treat.
Withdrawal criteria	
1.	Wishes to withdraw consent to participate in trial
2.	Move outside study *Woreda*
3.	Experiences of SAEs considered by trial coordinator to compromise ability to participate
4.	Experiences of SUSAR

### Sensitisation and recruitment procedures

The Rapid Ethical Assessment (REA) has been used prior to other studies to establish the most appropriate way of working with podoconiosis communities in southern Ethiopia [14] and Cameroon, and we plan to use this method in Gojjam before the trial. Rapid Ethical Assessment is a form of ethnographic assessment through which information about a community’s views and perspectives on specific research may be elicited and used to inform, for example, development of sensitisation approaches or consent processes [15]. Our sensitisation and recruitment will be modelled on the results of the REA, and the format of Information Sheets and Consent Forms will depend on responses given by participants in the REA. Written informed consent will be obtained from each participant.

### Community engagement strategy

The clinical service arm of the IOCC Podoconiosis Project is complemented by extensive community education and mobilisation aimed at decreasing misconceptions about disease aetiology and transmission, and stimulating awareness of ways of preventing and treating podoconiosis [11]. In addition, a community sensitisation workshop involving political, community and religious leaders, government representatives and local health workers will be conducted. These groups will play an important role in disseminating information about the trial and will act as the first level of ‘gatekeeping’ to the participants. Engagement with the community will continue throughout the trial via the Patient Associations (PAs).

### Sample size

We calculated the required sample size based on a mean (Standard Deviation) baseline incidence of ADLA of 5.6 (4.9) episodes/year reported in a survey conducted in November 2011 in this population [11]. We assumed a reduction in ADLA frequency of 28 % (from 5.6 to 4.0 episodes per year). Based on a sample size calculation for comparison of two means [16], a 90 % power, an α-level of 0.05, and a 40 % increase to enable adjustment for four confounders, and 15 % drop-out rate [9], that is, adjusting the sample size per group (206 × 1.4/0.85), we would need a total 680 patients: 340 patients in the immediate treatment arm and 340 patients in the control arm.

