### Statistical methods

Statistical support will be provided by the KEMRI-Wellcome Trust Programme in Kilifi, Kenya. A detailed Statistical Analysis Plan will be developed in 2014-15 while the intervention is in process, and will be approved by the Trial Steering Committee. The main analysis will be a test of mean number of ADLA events by each arm over the observation period.

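### The 40% sample-size inflation for four confounders has no basis in an individually randomised trial; on the protocol's own inputs 680 patients give about 97% power, and 90% needs about 486

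*Protocol article*

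**What the plan says.** The Sample size section of the protocol article starts from a "baseline incidence of ADLA of 5.6 (4.9) episodes/year" and states: "We assumed a reduction in ADLA frequency of 28 % (from 5.6 to 4.0 episodes per year". The method is given as "Based on a sample size calculation for comparison of two means", with "a 90 % power, an α-level of 0.05". Two allowances follow: a 40% "increase to enable adjustment for four confounders" and a "15 % drop-out rate". The section prints the combination, 206 × 1.4/0.85 per group, and concludes that 340 patients per arm, 680 in total, are needed. It does not name the four confounders or say where the 40% comes from.

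The abstract describes the trial as individually randomised. The Statistical methods section says of the analysis: "The main analysis will be a test of mean number of ADLA events by each arm over the observation period". It mentions no covariates there and leaves the detail to a statistical analysis plan that was still to be written.

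**The concern.** Confounding of the treatment comparison by baseline covariates is what randomisation removes in expectation. An allowance for adjustment makes sense in an observational comparison, where exposure and covariates are correlated and adjustment costs precision. In a randomised comparison of means that correlation is close to zero, and adjusting for prognostic baseline covariates usually keeps or improves precision. The largest multiplier in the calculation therefore rests on a reason that does not apply to this design. The section describing the main analysis also names no adjustment that would call for it.

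What is at stake is an accurate account of what the trial can detect. A reader takes 680 as the number needed for 90% power at a 28% reduction. On the stated inputs that is not so, and the trial's real margin is hidden behind an unsuitable reason. Someone planning a similar trial could also copy the multiplier.

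**Working it through.** **Inputs** (all from the Sample size section): control mean 5.6 and SD 4.9 episodes a year; reduction 28%, so δ = 0.28 × 5.6 = 1.568 (1.6 if the rounded 4.0 is used); power 90%; α 0.05; inflation 1.4; drop-out 15%. Sidedness is not stated. Two-sided is inferred because it reproduces 206, whereas one-sided gives 168 (or 161 with δ = 1.6).

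**1. Reproduce the protocol's figure.** Per group, n = 2(z₀.₉₇₅ + z₀.₉₀)² SD²/δ².
- δ = 1.568: 2 × (1.96 + 1.2816)² × 4.9²/1.568² = 205.2, rounded up to 206. This matches.
- δ = 1.6: 197.1, rounded up to 198.
- 206 × 1.4/0.85 = 339.3, rounded up to 340 per arm, 680 in total. This matches.

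**2. Size without the 1.4.** 206/0.85 = 242.4, rounded up to 243 per arm, 486 in total. The difference is 680 − 486 = 194 patients, or 194/680 = 29% of enrolment.

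**3. Power at 680.** Analysed per arm: 340 × 0.85 = 289. Standard error of the difference: 4.9 × √(2/289) = 0.4076.
- δ = 1.568: 1.568/0.4076 − 1.96 = 1.887, power 97.0%.
- δ = 1.6: 1.6/0.4076 − 1.96 = 1.965, power 97.5%.
- The noncentral t distribution gives the same values to within 0.1 percentage point.

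**4. Difference detectable with 90% power at 680.** (1.96 + 1.2816) × 0.4076 = 1.32 episodes a year; 1.32/5.6 = 23.6%.

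**5. What adjustment could cost under randomisation.** If arm and covariates have squared multiple correlation R², the variance of the treatment effect is multiplied by 1/(1 − R²), before any gain from explained outcome variance. A factor of 1.4 would need R² = 1 − 1/1.4 = 0.29. With four covariates and 2 × 289 = 578 analysed patients, the R² expected by chance is 4/577 = 0.007, a factor of 1.007. Applied to the base figure, 206 × 1.007 = 207.4 per arm, against 206 × 1.4 = 288.4. The protocol does not say that 1.4 was derived this way; the step only shows how large an allowance of this kind could reasonably be.

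**6. How far the margin reaches.** With 289 analysed per arm, power stays at 90% or more up to an SD of 1.568/(√(2/289) × 3.2415) = 5.8 (5.9 with δ = 1.6), instead of the assumed 4.9.

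**The case against.** The strongest reply is that nothing has been miscalculated. The 90% is an input, 206 follows from it exactly, and the 40% is shown openly. The protocol nowhere says that 680 patients give exactly 90% power in an unadjusted test. All of this stands. A reader might infer that the stated power is an arithmetic error; the text does not support that. The 90% is a correctly computed target with a disclosed, conservative addition on top.

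Three other strong readings also go too far.
- **The main analysis is unadjusted.** The Statistical methods section names no covariates but does not rule them out. It defers the detail to the statistical analysis plan, and the Sample size section itself says that adjustment is intended. The point does not depend on this: adjusted or not, a difference in means from an individually randomised trial does not need the 40%.
- **The 1.4 is a variance-inflation factor.** That is one possible origin, but the protocol gives none.
- **The protocol claims that 28% is the smallest detectable effect.** It presents 28% as an assumption.

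It can also be said that the surplus is welcome, since the intervention is delivered in monthly group meetings and the SD may be larger than assumed. The surplus may well be useful, but the protocol does not give that reason. It states no intracluster correlation or contamination rate from which 1.4 could be derived.

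**Conclusion.** The point holds in this form: the reason given for the 40% does not apply to an individually randomised comparison of means, and the stated size does not follow from the stated target. On the protocol's inputs, 90% power for a 28% reduction needs about 486 patients. The planned 680 give about 97%, or 90% power for a 23.6% reduction.

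These figures assume an SD of 4.9 in both arms, a two-sided 5% test, 15% loss and independent observations. A larger SD or correlation within treatment groups would bring the 97% down.

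The error is conservative. It affects neither the validity of the primary test nor its type I error, and on the stated inputs power exceeds the target. The correction is worth making because it is cheap and changes what the reader is told the trial can detect.

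**What to change.** Keep 680; recruitment had already begun according to the Trial status section, and there is no case here for reducing it. In the Sample size section:
- Delete the confounder justification for the 40%.
- State that 340 per arm, or 289 after 15% loss, give about 97% power for a 28% reduction, or 90% power for a reduction of about 23.6% (1.32 episodes a year). Give the assumptions alongside: two-sided 5%, SD 4.9 in both arms, independent observations.
- Do not relabel the 40% as a clustering or contamination allowance unless an assumed intracluster correlation or contamination rate is given that supports it.

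If covariate adjustment is intended, the Statistical methods section should say so, so that the two sections agree; the choice of covariates can be left to the statistical analysis plan. The cost is one paragraph of wording, with no change to enrolment.

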### Randomisation

Initial community sensitisation through *woreda-* and *kebele-*level officials will be followed by Health Extension Workers enumerating patients in their respective *kebeles* selected for the study in the *woreda*. All patients identified by Health Extension Workers (HEWs) will be visited at home by a data collector and consent requested for preliminary evaluation against the inclusion and exclusion criteria. The data collector will record potential willingness to take part in the trial, Geographic Information System (GIS) coordinates of the house and local contact information (for example, *kebele* office, nearest mobile phone owner). Patients who appear to be eligible will then be given an appointment date for enrolment at the nearest health facility. At enrolment, all patients will be asked for full consent for the trial; be evaluated against inclusion and exclusion criteria once more, and ICT tests and baseline measurements will be carried out. Community Podoconiosis Assistants (CPAs), Data Collectors (DCs) and data supervisors assisted by the study coordinator and data manager, will enrol patients.

Data collectors will then map these patients by recording Geographic Information System (GIS) coordinates of their houses, generating a target list of approximately 850 potential trial participants and take consent to examine each listed patient. If more than one eligible patient is found in one household, one will be randomly selected using a lottery method. Using a sample frame of households within *kebeles*, a randomisation list will be prepared by statisticians at Kenya Medical Research Institute-Wellcome Trust Research Programme (KWTRP). Patients will be randomised in excess of the required sample size to allow for those who decline the invitation to participate or who are later found not to fulfil the inclusion criteria.

### Blinding

Given the nature of the intervention, the trial cannot be blinded. Although data collectors will be independent of those delivering treatment, they will be able to deduce the randomization status of participants when they see the supplies required for treatment. Similarly, statisticians conducting the analysis cannot be blinded. To minimise bias, an *a priori* analytical plan will be defined as the intervention is in progress and will be adhered to.

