Each patient randomised to the treatment arm will be allocated one bar of toilet soap (GIV international white) every month, and rate of use will be monitored at monthly meetings. In addition, patients will have dispensed 40 gm of Whitfield’s ointment sufficient for daily application for one month, will be asked to bring used tubes with any remaining ointment to their group meeting each month, and excess ointment will be recorded. Patients with stage 3 and greater podoconiosis will each receive two short-stretch (<80 % stretch) bandages for each affected foot, one to be worn while the other is being washed and dried. Under likely home conditions, it is anticipated that bandages will need replacement after approximately 6 months. However, the condition of the bandages will be checked at monthly group meetings, and replacements given as required. Patients receiving bandages will also be given temporary, loose-fitting shoes at the enrolment visit. All patients’ feet will be measured at 3 months (once the majority of the swelling is anticipated to have subsided), and they will be given a pair of strong, closed ‘trainer’ or leather shoes and two pairs of socks. Patients will be encouraged to wear shoes all day, every day, no matter what their activities, and will be shown how to clean and care for their shoes and socks. We anticipate that high quality shoes will last for the full year of the trial, while socks will require replacement after 6 months, but the condition of shoes and socks will be monitored through the monthly meetings. Soap, Whitfield’s ointment and bandages will be kept out of the reach of children in a plastic treatment box. Standard operating procedures fully describe the hygiene products, their storage and application to assure consistency between participants, healthcare workers and study visits.

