### Outcomes and measurement

The primary outcome is the total number of ADLA episodes during the 12-month follow-up period. ADLA episodes have been demonstrated to be a common complication of podoconiosis lymphoedema, occurring on average five times per year, and contributing to an average 4.4 days off work per episode [13, 17]. They are highly distinctive to patients, who in the study area, refer to these episodes as ‘*michader*’ (‘the blight that casts you down causing you to spend the night where it hit you’). Patients describe pain (in inguinal nodes or in the lower leg), swelling in addition to the ‘normal’ lymphoedema, and redness of the leg (sometimes as discrete longitudinal lines), chills (‘*birrd*’), anorexia and sometimes lower leg skin peeling towards the end of the episode. Considering most of the patients are unable to write, the trial team have designed the diary such that each patient marks a check mark (✓) or a dash (-) under the boxes corresponding to drawings showing a healthy patient (working in the field) and a patient experiencing acute attacks (shown in bed) for each day of the month. During the pilot phase, patients had no difficulty in marking the diaries based on their experiences of acute attacks. For the trial, patients will be trained to complete diaries at the outset and those who may have difficulty (including the elderly or visually impaired) will be requested to have their diaries filled by family members or neighbours who are able to read and write. In addition, diaries of patients in the immediate treatment group will be checked and collected at every monthly intervention meetings, whereas all diaries of patients in the control group will be checked for the first month and a random 10 % on subsequent months. Data collectors will discuss these diaries with patients at the quarterly data collection visit at home, and discrepancies between diary and recall will be reconciled.

All secondary outcomes will be measured following internationally validated scales where possible. Where no internationally validated scale is available, previously reported questionnaires will be used (Table 1).

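### For the leg-examination endpoints, the plan accepts that data collectors will learn the arm and names no measure against biased readings beyond their independence; partial masking would reduce that risk, though not remove it

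*Protocol article*

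**What the plan says.** The Blinding section opens with a statement that covers every endpoint: "Given the nature of the intervention, the trial cannot be blinded". It gives one safeguard on assessment, that "data collectors will be independent of those delivering treatment", and then concedes that "they will be able to deduce the randomization status of participants when they see the supplies required for treatment". The remedy it offers is about analysis: "To minimise bias, an *a priori* analytical plan will be defined as the intervention is in progress and will be adhered to".

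Table 1 (Endpoints) lists among the secondary endpoints clinical stage, "Lower leg and foot circumferences", mossy changes, and wounds and interdigital lesions. Table 3 (Study visits) schedules stage at baseline and at every quarterly visit, and circumference, mossy lesions and interdigital lesions at baseline and at months 6 and 12.

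Under Outcomes and measurement, "Data collectors will discuss these diaries with patients at the quarterly data collection visit at home". The Safety section has data collectors complete the adverse-event forms at the same quarterly home visits. The Intervention section says that soap, ointment and "bandages will be kept out of the reach of children in a plastic treatment box". It also has treated patients wear bandages (stage 3 and above) and the shoes and socks issued to them.

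**The concern.** The Blinding section treats all endpoints alike, but they are not equally exposed. Patients know what they receive, so the diary, quality of life, disability and stigma results cannot be shielded. The leg examination is different: an examiner grades or measures it, and it needs no statement from the patient about treatment. The cue the section names, the sight of supplies, can partly be managed by how the visit is run.

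The stated remedy also does not meet the stated problem. A fixed analysis plan limits the analyst's discretion. It does nothing about a stage graded more favourably because the examiner knew the arm.

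The primary outcome is recorded by patients in an open trial, so the examiner-read endpoints are useful corroboration. The Discussion also wants the timing of clinical changes related to psychosocial ones. Both uses weaken if examiners know the arm.

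**Working it through.** **1. The plan's own figure.** The documents give no calculation for the leg endpoints. The only sample size is for the primary outcome (Sample size section): SD 4.9, a 28% reduction from 5.6 (0.28 × 5.6 = 1.568), power 90%, α 0.05, taken as two-sided.

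n = 2 (1.960 + 1.2816)² × 4.9² / 1.568² = 2 × 10.508 × 24.01 / 2.4586 = 205.2, so 206 per group. Then 206 × 1.4 / 0.85 = 339.3, so 340 per arm and 680 in total. This reproduces the plan. Only the 340 and the 15% drop-out are used below: 340 × 0.85 = 289 analysed per arm.

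**2. What could reveal the arm, and when.** Reading Table 3 with the Intervention and Outcomes sections:

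| Cue | Can it be managed? |
|---|---|
| Soap, ointment, spare bandage in the box | Yes, put out of sight |
| Bandages, shoes and socks worn on the leg | Largely; the foot has to be bare for mid-foot circumference and interdigital inspection anyway |
| Diary discussion and adverse-event questions, every quarter; adherence questions, if asked | At that visit, yes, by examining first; at later visits, only if a different person examines |
| Look of washed or treated skin, remarks by the patient | No, or only in part |

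The third row matters most. Circumference, mossy lesions and interdigital lesions are first read after baseline at month 6. By then the month 3 visit has already covered diary and adverse events. Examining first, with the same collector throughout, would therefore protect only the month 3 stage reading. It has to be combined with rotation.

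**3. How much a reading shift could matter (illustration).** Assumptions: no true effect, a continuous measure, a two-sided 5% comparison of means, 289 per arm, and an average shift of b SD in favour of the treated arm. The shift is assumed; nothing in the documents supplies it.

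SE = √(2/289) = 0.0832 SD, λ = b / SE, and P(reject) = 1 − Φ(1.960 − λ) + Φ(−1.960 − λ). For b = 0.10, λ = 1.202.

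| b (SD) | 289 per arm | 340 per arm (no drop-out) |
|---|---|---|
| 0 | 5.0% | 5.0% |
| 0.05 | 9.2% | 10.0% |
| 0.10 | 22.5% | 25.6% |
| 0.15 | 43.8% | 49.8% |
| 0.20 | 67.2% | 74.1% |

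Incomplete masking would still be worth having: if it halved an average shift from 0.20 to 0.10 SD, the rate would fall from 67.2% to 22.5%.

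The formula fits circumference most directly. Stage is a graded scale and mossy changes are presence or absence, so for these the table shows only the direction and rough scale. No SD for circumference is given, so b cannot be turned into centimetres.

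**The case against.** The plan states nothing false here. It openly discloses a limitation of a pragmatic trial, keeps collectors separate from those who treat, and refers to operating procedures and case report forms that are not shown and may fix the order of assessments. Only secondary endpoints are touched. The percentages rest on assumed shifts and would be the same for any open trial of this size. All of that stands, and it limits the weight of the point.

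It does not dispose of the point. The article itself declares blinding impossible without distinguishing endpoints and names a remedy that acts on analysis, so this is a stated design choice rather than a detail left out.

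A reader might infer more than the documents support:

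- *That unblinding of the leg examination can be prevented by visit order and stowing supplies.* It cannot. Earlier visits can reveal the arm, and supplies are not the only cue.
- *That the treatment box hides everything.* It is described as a way to keep items from children, it is not said to be closed, and one bandage is meant to be worn.
- *That one collector demonstrably sees the supplies, discusses the diary and examines the legs.* The article places collectors at the quarterly visit "at the quarterly data collection visit at home" for diaries and adverse events. It does not say who examines the legs at follow-up; that collectors do so is the natural reading, but an inference.
- *That the leg findings are the only outcomes not self-reported.* Soap use is monitored and returned ointment recorded at the monthly meetings, so adherence is partly observed too.

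**Conclusion.** The point holds as a low-cost improvement to secondary endpoints. The Blinding section accepts assessor unblinding for every endpoint. Beyond the collectors' independence from treatment, its only answer is a plan that cannot remove measurement bias. This leaves a risk of assessor bias in stage, mossy changes and interdigital lesions, and a smaller one in tape-measured circumference. The risk could be reduced but not eliminated.

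It would go too far to say that these results carry bias. The documents support a risk, and they do not show its size. The 22.5% to 67.2% range depends wholly on assumed shifts of 0.10 to 0.20 SD, 289 analysed per arm and no true effect. The conclusion also assumes that data collectors do the leg examination. The primary outcome gains nothing from this change.

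**What to change.** In the Blinding section, confine the statement that blinding is impossible to participants, treatment providers and self-reported outcomes. For the leg examination at follow-up, identically in both arms:

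1. Supplies, bandages, socks and shoes are put away and the legs bared before the examiner sees the patient.
2. Stage, circumference, mossy changes and interdigital lesions are examined and recorded before the diary, adverse-event, adherence and questionnaire sections.
3. Data collectors are not given the allocation list.
4. Existing collectors are rotated, so that whoever examines at months 6 and 12 has not previously discussed the diary or adherence with that patient.
5. The examiner records a guess of the arm straight after the examination, and the results are reported by arm.

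If one collector does the whole visit, step 4 needs at least three per patient over the year: one for months 3 and 9, a second for month 6, a third for month 12. The month 9 stage reading then stays less protected. The article speaks of several collectors but gives no number, so this should be checked against staffing.

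The cost is reordered form pages, a paragraph in the operating procedures, one extra item and some scheduling. Sample size, α, the intervention and visit dates do not change, and no extra staff are needed if the existing collectors can be rotated. Masking will be incomplete, and the guess item will show by how much.
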